### Randomisation

Sites were randomly assigned in a 1:1 ratio to either the intervention group or the control group. Randomisation was based on a minimisation algorithm that considered the state, facility level (primary, secondary and tertiary) and empirical postpartum use of antibiotics. Randomisation was undertaken by the statisticians, and the health facilities were informed of their random allocation before any participants were assessed for eligibility.

### Blinding

Due to the nature of the intervention and the cluster trial design, sites are not blinded to randomised allocation. The independent trial statistician will have access to blinded data until database lock to support the DSMB and the Trial Steering Committee (TSC).

### Data collection

Study participants are enrolled in labour and followed up with visits at 3 days, 2 weeks, 4 weeks and 6 weeks postpartum (table 3). To minimise missed visits and loss to follow-up, counselling sessions are extended to partners and family members when necessary and during follow-up visits. Reminders for follow-up appointments are sent via short message service and telephone. The details of participants’ home addresses are also collected at enrolment and updated during each visit. For participants who cannot be reached, community tracking will be done (a home-based monitoring system designed to locate participants in their homes). Consent for home visits and community tracking is obtained at enrolment.

**Table 3 T3:** Schedule of activity

Study epoch	Antenatal	Labour	Postpartum				
Visit number	0	1a	1b	2	3	4	5
Time in study	ANC visits	During labour	After delivery, before discharge	3 days	2 weeks	4 weeks	6 weeks
Assessment window/study procedure			+12 hours	±1 day	±3 days	±5 days	±7 days
Awareness and sensitisation	X						
Counselling and provision of participant’s information leaflet	X	X					
Screening for eligibility		X					
Informed consent		X					
Assign study ID number		X					
Study intervention (AZM or usual care)		X					
Vital signs		X	X	X	X	X	X
Clinical lab evaluation*		X	X	X	X	X	X
Baseline information (mother) (sociodemographic, clinical, medical history, labour and delivery information, etc)		X	X				
Baseline newborn information (sex, birth weight, birth outcome, complications, etc)			X				
Maternal outcomes		X	X	X	X	X	X
Neonatal outcomes			X	X	X	X	X
AEs		X	X	X	X	X	X
Cost-effectiveness information		X	X	X	X	X	X
Participant EOS							X

Participants who booked for ANC will be counselled/consented during the antenatal period and consented/reconsented in labour.

* Clinical lab evaluation includes full blood count; electrolyte, urea and creatinine; procalcitonin; malaria parasite and microbiology culture as indicated.

AE, adverse event; ANC, antenatal care; AZM, azithromycin; EOS, end of study.

REDCap (Research Electronic Data Capture V.13.8.3, Vanderbilt University, Nashville, Tennessee, USA) is used to collect all relevant study data. Designated investigators and study staff will enter trial data using password-protected electronic devices. Outcome data are collected during labour and childbirth and up to 42 days postpartum. Baseline sociodemographic data are also collected.

In the case of suspected maternal and/or neonatal infection, participants are invited to the facility for detailed assessment and sample collection by the clinician, with relevant biological specimens collected: peripheral blood for blood culture, full blood count, blood film, malaria parasite, electrolytes, urea and creatinine, liver function tests and procalcitonin; midstream urine for microscopy, culture and sensitivity (MCS) and wound (perineal or caesarean) swab, drained abscesses swab, stool, sputum or tissue samples for MCS as appropriate. Microbiological samples are collected aseptically from the mother and newborn at multiple follow-up points, as required. These samples are cultured to identify bacterial species.

Maternal antibiotic usage data are also recorded, covering study and non-study antibiotics administered before birth, during the hospital stay and after discharge, up to 42 days postpartum to capture the full scope of antimicrobial exposure. Any AEs related to the intervention or pregnancy and childbirth are documented to monitor safety. All clinical and laboratory data are securely managed via an electronic data capture system (REDCap) with centralised quality control measures to ensure accuracy and consistency.

### Statistical methods and analysis

All analyses will be intention-to-treat unless specified. Categorical variables will be summarised as frequencies and percentages. Continuous variables will be presented with N (number of observations), means (SD) and/or medians (IQRs), depending on whether they are normally distributed. The primary outcome will be analysed using a random effects logistic regression model to estimate the treatment effect with 95% CI. The model will be adjusted for the stratification variables, along with any imbalance in key baseline variables. The secondary outcomes will be analysed using random-effects models depending on the distribution of the outcome. Missing data will be described explicitly with the number reported for each variable, and where appropriate, multiple imputation methods may be employed. An interim analysis will be conducted at the halfway point through the trial (50% of the target sample with the primary outcome). If the p value indicates an overwhelming effect (as evidenced by a p value less than 0.001—the Haybittle-Peto rule),^49^ the DSMB may request unblinding, and a recommendation to stop the trial may be considered.

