### Research governance

The TMG is responsible for ensuring high-quality delivery of the trial in accordance with the protocol and addressing problems promptly. The TMG includes the chief investigator, coinvestigators, trial manager and data manager. The TMG reports to the independent TSC and the independent DSMB. The TSC will provide independent oversight and advice to the trial, while the DSMB is responsible for monitoring the trial data, including safety and data integrity. The independent DSMB will monitor all SAEs and review SAE events by masked treatment group at each meeting and report to the TSC. The DSMB will consist of a global health physician ([name], Harvard T.H. Chan School of Public Health, USA), a paediatrician ([name], University of Calabar, Nigeria) and a medical biostatistician ([name], London School of Hygiene and Tropical Medicine, UK). Auditing of research records will be conducted by the monitoring committees as outlined above, while financial auditing will be conducted by the Research Management Office and the Audit Department of the University of Lagos.

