This research protocol acknowledges the essential clinical responsibilities of health facility staff involved in the study, particularly in data collection and administration of the investigational drug to enrolled participants. To minimise disruption to their routine clinical duties, the following measures were implemented: (1) two trained research nurses are assigned per facility to assist with research tasks (data collection and participant tracking/follow-up) to ease the workload of regular clinical staff; (2) research activities are scheduled in coordination with facility management to avoid peak clinical hours and ensure uninterrupted patient care; (3) facility clinical staff’s participation in research is limited, clearly communicated and will not extend beyond their agreed working hours; (4) continuous monitoring is carried out to promptly identify and address any negative impact of research activities on clinical workflow and patient care and (5) participation of clinical staff in research tasks is voluntary, with the option to withdraw at any time without negative consequences.

Confidentiality of data obtained from participants will be maintained throughout the trial. All data collected at the study sites on REDCap are stored centrally in a password-protected electronic database by the senior data manager, who is the only person with access to the blinded data of all participants, collated centrally. Any approved modification to the protocol will be communicated to the investigators, and retraining of study staff on the amended protocol will be done as necessary.

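### The DSMB sees SAEs only by masked group, and the one written unblinding trigger is a directionless p<0.001 that asks as much evidence of harm as of benefit

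*Protocol article*

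**What the plan says.** Five statements in the protocol article bear on this.

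- Research governance: "The independent DSMB will monitor all SAEs and review SAE events by masked treatment group at each meeting and report to the TSC".
- Blinding, on the statistician: "The independent trial statistician will have access to blinded data until database lock to support the DSMB" and the steering committee. On sites, the same section says "sites are not blinded to randomised allocation".
- Statistical methods and analysis, on timing: "An interim analysis will be conducted at the halfway point through the trial (50% of the target sample with the primary outcome"). Only this one look is described.
- The same section, on the rule: "If the p value indicates an overwhelming effect (as evidenced by a p value less than 0.001—the Haybittle-Peto rule"), "the DSMB may request unblinding, and a recommendation to stop the trial may be considered". It states no direction and no separate boundary for harm.
- Ethical considerations: the central database is kept by the senior data manager, "who is the only person with access to the blinded data of all participants, collated centrally".

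Adverse drug event monitoring adds channels that do not depend on the interim p value. Site investigators grade each event for its relationship to the drug. SAEs go to the Principal Investigator, who notifies the sponsor and the ethics committee. Serious unexpected reactions go to the national regulator. Other independent safety monitors share oversight with the DSMB.

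**The concern.** A safety board weighs an excess of events on the new treatment differently from an excess on usual care. Suppose masked tables show sepsis in 9% of one group and 6% of the other. Either azithromycin cuts sepsis by a third (6/9 = 0.67) or it raises it by half (9/6 = 1.5). The first is a reason to carry on, and the second may be a reason to pause. The article does not give the board what it needs to tell them apart.

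The one written way to learn the direction is a p value below 0.001. That level suits stopping for benefit, where an early claim must be hard to make. It is a demanding level for harm, and the rule does not separate the two. The interim appears to concern the primary outcome, so maternal death, stillbirth, neonatal death and SAEs have no written unmasking provision.

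The data-access statements also do not fit together. If the supporting statistician stays blinded until database lock, the article names nobody who could answer an unblinding request at the interim. If the senior data manager is the only person with the blinded data of all participants, the independent statistician cannot also have them.

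**Working it through.** **Inputs** (Sample size, Randomisation, Statistical methods and analysis): 6.5% against 3.25%; 90% power; 5% level; ICC 0.011; 20% loss; 48 facilities allocated 1:1, so 24 per arm; about 105 women per facility; one interim at 50%; p<0.001. Assumed: two-sided tests, an interim p value on the primary outcome, and an interim sample spread evenly over facilities.

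**The plan's own sample size**

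- Two proportions, pooled: n = [1.96·√(2p̄q̄) + 1.2816·√(p₁q₁ + p₂q₂)]² / (p₁ − p₂)², with p̄ = 0.04875. This gives 921 per arm.
- Design effect: 1 + (105 − 1) × 0.011 = 2.144, and 921 × 2.144 = 1,975.
- Loss: 1,975 / 0.80 = 2,469 per arm, against 2,520 stated (24 × 105 = 2,520). The difference is about 2%, so the figure reproduces.

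**Effective size at the interim**

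- Half of the enrolment target: 1,260 per arm, 52.5 per facility. Design effect 1 + 51.5 × 0.011 = 1.5665. Effective n = 1,260 / 1.5665 = 804 per arm.
- Half of the evaluable sample: 2,520 × 0.8 / 2 = 1,008 per arm, 42 per facility. Design effect 1 + 41 × 0.011 = 1.451. Effective n = 1,008 / 1.451 = 695 per arm.

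**Chance of meeting p<0.001**

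Probability = Φ{(|p₁ − p₂| − z·√(2p̄q̄/n)) / √((p₁q₁ + p₂q₂)/n)}, with z = 3.29 for two-sided 0.001.

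For 9.75% on azithromycin (risk ratio 1.5) and n = 804, p̄ = 0.08125. The pooled standard error is √(0.1493/804) = 0.01362, so the threshold is 3.29 × 0.01362 = 0.0448. The unpooled standard error is √(0.1488/804) = 0.0136. The result is Φ{(0.0325 − 0.0448)/0.0136} = Φ(−0.91) = 0.18.

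| Sepsis on azithromycin (6.5% in control) | n = 804 | n = 695 |
|---|---|---|
| 3.25% (planned benefit) | 0.40 | 0.32 |
| 9.75% (risk ratio 1.5) | 0.18 | 0.14 |
| 13% (risk ratio 2.0) | 0.87 | 0.79 |
| Rate for an even chance | 11.2% (1.72) | 11.6% (1.78) |
| Rate for an 80% chance | 12.5% (1.93) | 13.1% (2.01) |

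For scale only, at z = 1.96 a risk ratio of 1.5 would be flagged with probability 0.67 (n = 804) or 0.60 (n = 695).

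These figures describe the primary-outcome trigger. The article applies no p value rule to SAEs, deaths or neonatal outcomes, so none is computed for them.

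**The case against.** The strongest reply is that the interim rule sits in a statistics section and says only what may follow one look at the primary outcome. It does not bar unmasking on other grounds. Research governance separately makes the DSMB responsible for safety monitoring, and rules for closed reports and harm commonly sit in a charter or full protocol that is not shown. Masked tables would still show an imbalance at each meeting, and the board could discuss it, ask for the codes or advise the steering committee. Masked review and a symmetric boundary are also recognised design choices.

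Much of this stands. A reader might infer that p<0.001 is the only permitted route to unmasking, or that harm cannot be told from benefit. The text supports neither: it is the only route written, nothing forbids another, and the adverse-event section supplies partial information. Nor can one say that the board could work out the arms from its tables, because the article does not say whether those tables identify facilities.

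The reply does not remove the point. Masked SAE review, blinded data for the supporting statistician until lock, and a directionless threshold are rules the article states, not details it leaves out. Information that reaches the board through unblinded site investigators is a poor substitute for a planned report by arm. With sites already open, masking the board protects little.

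On data access, a reader might infer that a member of the trial management group holds the data. The group includes a data manager, but the article does not say that this is the senior data manager who keeps the database. Both statements also concern blinded data. What remains is a conflict of wording over who has access.

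**Conclusion.** The point holds as a badly fixed monitoring rule that wording can repair. As written, the board is not given the direction of a safety imbalance, and the one stated trigger asks for the same extreme evidence in either direction. A true 1.5-fold rise in sepsis would meet it about 14% to 18% of the time, and about a doubling is needed for an 80% chance.

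This rests on the 6.5% control rate and ICC of 0.011 in the sample size section, even recruitment over 48 facilities, and a two-sided interim test of the primary outcome. It does not show that a moderate harm would go unnoticed or undiscussed. A charter that already provides reports by arm and a harm criterion would settle most of it, but the article's statements would still need to agree with that charter and with each other.

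**What to change.** 1. **Research governance and Blinding:** state that the DSMB receives SAE, death and interim tables by arm in closed session from its next meeting, prepared by the independent statistician. Keep the trial management group and the steering committee masked to comparative data.
2. **Statistical methods and analysis:** state that p<0.001 governs stopping for benefit only, and that the DSMB judges harm on its own, less extreme criterion, to be set by the board.
3. **Ethical considerations:** reword the claim of sole access so that it agrees with the Blinding section, and say who holds data by arm.

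The change is to protocol and charter wording. It slightly raises the chance of a pause from a chance imbalance and adds no type I error for benefit. It should be made promptly, since Trial status projects that recruitment will end by March 2026.

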### Cost-effectiveness analysis

An Incremental Cost-Effectiveness Ratio (ICER)—the additional cost per unit of health gain with AZM compared with usual care for individual participants as a component of the sepsis prevention protocol in healthcare facilities—is included.

Cost data related to birth and associated healthcare services are collected from both participants and health facilities involved in the study. From participants, cost data are collected after birth through structured interviews conducted before discharge and during any postpartum visits, up to 42 days. The data will include out-of-pocket expenses for birth consultations, medications, laboratory tests, hospital stays, transportation and any other costs incurred due to maternal or neonatal care, especially those related to AEs or complications. From the 48 health facilities of this clinical trial, cost data are collected through interviews and records review, involving facility managers, healthcare staff, administrators, laboratory scientists, pharmacists and other relevant personnel. This will cover direct and indirect costs associated with delivering care, including staff time, consumables, medications, laboratory and diagnostic services, infrastructure uses and overhead costs. Data on service utilisation, resource allocation and administrative expenditures relevant to maternal and neonatal care during the study period are extracted from facility records. This dual approach will enable a comprehensive estimation of the cost-effectiveness of the intervention from both patient and provider perspectives.

We will conduct a cost-effectiveness analysis to compare the costs and health benefits associated with AZM intervention compared with the usual care in reducing maternal sepsis among pregnant women undergoing vaginal birth from both patient and health provider perspectives. Cost elements for both arms will be comparatively assessed at an individual participant level, using a decision tree. Comparative analyses of the direct medical costs of the intervention and usual care, including the costs of administering a full course of treatment with both products (medicines, consumables and supplies), will be included. Analysis of all costs borne by participants from potential AEs and any loss of productivity while incapacitated by these AEs will be conducted for the study population (all enrolled women in the clinical trial). The ICER will be obtained from the mean values of costs and effectiveness. The CI for the ICER will be derived using non-parametric bootstrapping to quantify sampling uncertainty. Incremental costs and utilities in disability-adjusted life years averted will be determined as part of a cost-utility analysis. Uncertainty will be addressed by a univariate sensitivity analysis. In addition, a probabilistic sensitivity analysis, in which all parameters with uncertainty will be varied within their CIs, will be used to establish a credible interval for the estimated result.

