### Adverse drug event monitoring

Adverse events (AEs), including serious AEs (SAEs), are closely monitored and recorded on the electronic case report form throughout the duration of the trial, in accordance with Good Clinical Practice guidelines and all applicable regulatory requirements. At each study visit, participants are evaluated for AEs and asked about any symptoms that have occurred between study visits. Participants are advised and requested to report symptoms suggestive of AEs. An AE is defined as any unfavourable or unintended medical occurrence in any participant who has received the trial drug or usual care, regardless of whether it has a causal relationship with the intervention. SAE is defined as any event that (1) results in death; (2) is life-threatening; (3) requires hospitalisation or prolongation of existing hospitalisation; (4) leads to persistent or significant disability or incapacity or (5) constitutes a congenital anomaly/birth defect. AEs are documented according to the severity, duration, grade, relationship to trial drugs, interventions given and outcome. The costs of treating all adverse drug events related to trial drugs will be borne by the trial. Each AE/SAE is assessed by the site investigator for severity, expectedness and its relationship to the trial drug or study procedure (unrelated, unlikely related, possibly related, probably related or definitely related). All SAEs are reported to the Principal Investigator, who will, in turn, notify the trial sponsor and the Institutional Review Board/ethics committee in accordance with local regulatory requirements. Any serious, unexpected adverse drug reactions will also be reported promptly to the national drug regulatory authority in line with pharmacovigilance requirements. All study participants with AEs are managed and followed up until the resolution or stabilisation of the AE. Where necessary, additional medical information is obtained to ensure a comprehensive evaluation of the AE. Safety oversight during the trial is provided by a Data and Safety Monitoring Board (DSMB) and other independent safety monitors.

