### Sample size

A sample size of 5040 (2520 in each group) is required to detect a 50% reduction in the maternal sepsis incidence rate from 6.5% to 3.25% due to AZM, at 90% power and a 5% level of significance. The sample size accounted for an intraclass correlation (ICC) of 0.011 and 20% loss-to-follow-up. The incidence rate of sepsis or severe systemic infection was found to be 6.5% in a study of maternal near-misses at the University of Port Harcourt, Rivers State, Nigeria.^47^ In a randomised clinical trial (RCT) of AZM versus placebo in Burkina Faso and The Gambia, the OR of maternal sepsis was 0.62 for any maternal sepsis and ~0.00 for bacterially confirmed sepsis.^25^ The incidence of sepsis in this study was much lower than in our setting (0.2% vs 6.5%). The ICC was derived from an analysis of the WHO Global Survey on Maternal and Perinatal Health.^48^ We require 48 health facilities and estimate each will enrol approximately 105 participants per facility within 10–12 months on average.

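### Trial-paid treatment of azithromycin adverse events drops out of the patient-perspective ICER, and the ICER bootstrap does not say that facilities are resampled

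*Protocol article*

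**What the plan says.** **Adverse-event costs.** The section on adverse drug event monitoring says: "The costs of treating all adverse drug events related to trial drugs will be borne by the trial". Under Cost-effectiveness analysis, the patient side consists of out-of-pocket spending collected by interview, and the plan announces "Analysis of all costs borne by participants from potential AEs", together with productivity lost through those events. The provider side comes from interviews and records at the 48 facilities and covers items such as staff time, medicines and laboratory services. Both perspectives are to be reported. The Control section says that control sites are not supplied with azithromycin. The Introduction puts out-of-pocket payment above 70% of health expenditure in Nigeria and gives this financing context as one reason why local evidence is needed.

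**Interval for the ICER.** The Cost-effectiveness analysis section says: "Cost elements for both arms will be comparatively assessed at an individual participant level, using a decision tree". The ICER is taken from mean costs and mean effects, and: "The CI for the ICER will be derived using non-parametric bootstrapping to quantify sampling uncertainty". The section mentions neither clusters nor a resampling unit. Elsewhere clustering is recognised. Facilities are the randomised units (Randomisation), "The sample size accounted for an intraclass correlation (ICC) of 0.011 and 20% loss-to-follow-up", and the primary and secondary clinical outcomes are analysed with random-effects models (Statistical methods and analysis).

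**The concern.** Cost-effectiveness is a stated objective and is meant to inform policy. Two features of the economic text could distort it.

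First, what a woman pays for a drug-related adverse event inside this trial is not what she would pay in routine use. The trial's payment rule removes the treatment bill, and the analysis counts only what she bears. Only one arm receives the trial drug, so the omission does not cancel between arms.

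Second, the interval method is fixed without the feature of the design that determines its validity. Women at the same facility share its practices, and where facility overheads are applied as common unit costs they share those too. A bootstrap that treats women as independent would give too narrow an interval. The planned probabilistic sensitivity analysis varies parameters within their confidence intervals, so any interval that was too narrow for this reason would carry the error forward.

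**Working it through.** **1. Adverse-event costs: the rules side by side**

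| Component of adverse-event cost | Who bears it under the protocol | Counted in patient perspective? |
|---|---|---|
| Treatment of drug-related events | the trial | no, as written |
| Treatment of unrelated events | the woman or the facility, as usual | yes, where she pays |
| Transport and other spending | the woman | yes |
| Lost productivity | the woman | yes |

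The first row can arise only in the azithromycin arm. Let q be the number of treated drug-related events per woman in that arm and c the mean amount she would have paid per event in routine care. Incremental patient cost is then understated by q × c per woman, and the ICER by q × c / ΔE, where ΔE is sepsis risk averted per woman.

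At the planning effect ("from 6.5% to 3.25% due to AZM"), ΔE = 0.065 − 0.0325 = 0.0325 and 1/0.0325 = 30.8. Each currency unit omitted per woman would therefore lower the cost per sepsis case averted by about 31 units. The document gives neither q nor c, so the shift itself cannot be computed.

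**2. The plan's own sample size**

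This is the only stated figure that bears on clustering. Inputs from the Sample size section: 6.5% and 3.25%, "at 90% power and a 5% level of significance" (two-sided assumed), ICC 0.011, 20% loss, and 105 women in each of 48 facilities (24 per arm).

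- Individually randomised: n = [1.960 √(2 × 0.04875 × 0.95125) + 1.282 √(0.065 × 0.935 + 0.0325 × 0.9675)]² / 0.0325² = 921 per arm.
- Design effect: 1 + (105 − 1) × 0.011 = 2.144, and 921 × 2.144 = 1,975.
- Loss: 1,975 / 0.80 = 2,469 per arm.

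The plan says "A sample size of 5040 (2520 in each group) is required". The computed figure is within 3% of this, and 24 × 105 = 2,520 exactly. The plan's figure therefore already carries a design effect of about 2.

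**3. What ignoring facilities would do to the interval**

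The SE factor is √(1 + (m − 1) × ICC). Coverage of a nominal 95% interval that ignores clustering is 2Φ(1.96/factor) − 1. Cluster size m is 105 as enrolled, or 105 × 0.80 = 84 after loss.

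| ICC | Source | m | Design effect | SE factor | Coverage |
|---|---|---|---|---|---|
| 0.011 | protocol | 84 | 1.91 | 1.38 | 84% |
| 0.011 | protocol | 105 | 2.14 | 1.46 | 82% |
| 0.005 | assumed, costs | 84 | 1.42 | 1.19 | 90% |
| 0.02 | assumed, costs | 84 | 2.66 | 1.63 | 77% |
| 0.05 | assumed, costs | 84 | 5.15 | 2.27 | 61% |
| 0.10 | assumed, costs | 84 | 9.30 | 3.05 | 48% |

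At ICC 0.011 the interval would have 72% (m = 84) to 68% (m = 105) of its proper width.

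A simulation of the incremental effect with 24 facilities per arm, 84 women each and ICC 0.011 gave 84% coverage with individual-level standard errors and 93% with facility-level ones. It used analytic standard errors in place of resampling.

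**The case against.** **On the bootstrap**, the objection is strong. A cluster or two-stage bootstrap is also non-parametric, so the text as written permits it. The phrase about the individual participant level describes how cost elements are assessed, not how resamples are drawn. A condensed article may leave the resampling unit to the full protocol or the analysis plan, and this trial handles clustering properly in its sample size and clinical models. A reader might infer that the interval will be too narrow. The document does not support that: it is silent, and the figures above hold only if facilities are ignored. They also describe a mean difference under a normal approximation. An ICER depends as well on the variance of costs and the cost–effect covariance, so they are not coverage figures for the ICER itself. What remains is that the article fixes an interval method for a stated objective and omits the one clause that would make it valid for this design.

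**On adverse-event costs**, a reader might infer that such costs are near zero in the azithromycin arm. That also goes too far, because transport, lost productivity and treatment of unrelated events are still collected. Facility records may pick up staff time, medicines and tests used in treating drug-related events, whoever pays. The named drug events are fainting or dizziness, nausea, vomiting, diarrhoea and dyspepsia after a single dose, so the sums may well be small. These points limit the size of the problem. They do not remove the conflict in the patient perspective, where both the payment rule and the costing rule are stated and nothing says that trial-paid care will be valued and added back.

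**Conclusion.** The adverse-event point holds on the text. Following the stated rules removes the treatment cost of azithromycin-related adverse events from the patient-perspective ICER, in one arm only and in azithromycin's favour. It is an artefact of trial conduct. Its size is unknown and probably small, and it may be partly captured from the provider perspective.

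The bootstrap point holds as a conditional one. The plan neither specifies nor rules out resampling of facilities. If women alone were resampled, the standard error of the incremental effect would be understated 1.38- to 1.46-fold and coverage would be about 84% to 82%, at the protocol's ICC for the primary outcome and 84 to 105 women per facility. The corresponding loss for costs cannot be stated, because no cost ICC is given. The range shown for 0.005 to 0.10 is assumption, and nothing in the document shows that costs vary mainly between facilities.

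Neither point touches the primary clinical analysis.

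**What to change.** 1. **Reconcile the adverse-event monitoring and cost-effectiveness sections.** State that adverse-event care paid for by the trial will be identified from trial payment records, valued at routine user prices for the patient perspective or at facility prices for the provider perspective, and added to the azithromycin arm. State also how care already captured in facility records will be kept from being counted twice. Azithromycin costs become slightly higher.

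2. **Name the resampling unit.** State that facilities are resampled within arm (cluster or two-stage bootstrap), with each woman's cost and effect kept as a pair. The interval may be wider. If the full protocol or analysis plan already specifies this, one clause in the article settles it.

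Incremental net benefit and an acceptability curve would be useful beside the ICER, whose interval is hard to interpret when the effect difference spans zero, but they are optional reporting.

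The cost is wording, programming and retrieval of the trial's payment records. No additional participants and no change in trial conduct are needed.
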